Current research in HDP focuses on re-proving old and commonly used homeopathic remedies in double-blinded and placebo-controlled trials. In these studies blinded homeopaths were asked to identify drug-specific symptoms in the diary of each study-subject and assign them to a list of potential homeopathic drugs. In the last blinded HDP conducted by this study group, two well-known homeopathic remedies (Natrium muriaticum and Arsenicum album) were tested against placebo. The blinded homeopaths identified only Arsenicum album-specific symptoms in the Arsenicum album group, only Natrium muriatricum specific symptoms in the Natrium muriaticum group and only non-specific symptoms in the placebo group. The results of this and a previous HDP showed that specific symptoms of the HDP could be identified and allocated by blinded raters with a high statistical significance [8,9,11]. To our knowledge, it is not clear whether the identification of drug-specific symptoms may also be achieved for new and unknown homeopathic drugs. Therefore, in our opinion, a key question of current HDP research is to define specific symptoms, including a list of criteria, and to develop a qualitative analysis method in order to identify them in new and unknown homeopathic drugs.

Homeopaths and researchers have developed a variety of study protocols for HDP and incorporated a variety of modern standards in the last few years [2,3,12-16].

National and European authorities require that the Guidelines for Good Clinical Practice (ICH GCP), the Declaration of Helsinki and the national drug regulations be applied for HDP and methodological and legal consequences must be considered. The European Committee for Homoeopathy (ECH) developed the "Homoeopathic drug proving guideline" [2] which for the first time, adapts traditional HDP methodology to the requirements of modern European standards. German drug regulations have meanwhile classified HDP as clinical phase 1 trials. Within this study we developed, for the first time, a study design methodology and a study-protocol that fulfils the criteria of a phase-1-trial, GCP, Declaration of Helsinki and German drug regulations and also tests its applicability and feasibility in practice. The main aim of the study is to determine whether a homeopathic drug in the potency C12 provokes more characteristic homeopathic proving symptoms after three weeks compared to a placebo in healthy volunteers. Therefore our hypotheses to test are:

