### Outcome parameters

The primary outcome parameter is the number of characteristic proving symptoms per subject, derived from the qualitative data analysis of the homeopathic proving drug compared to placebo within three weeks after the initial dose of the drug or the placebo is administered. Definitions of characteristic symptoms are given in Table 1.

Secondary outcome parameters are: the total number of proving symptoms irrespective of whether they are characteristic or not (definition of proving symptoms see Table 1) and the number of serious adverse events.

Qualitative differences in the profiles of characteristic proving symptoms from the homeopathic drug and the placebo will also be compared and the inter-coder reliability of the qualitative evaluation of characteristic proving symptoms will be calculated.

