**Figure 3 F3:**
[figure not shown]
**Data analysis process in homeopathic drug proving trial**.

After closing the trial, the investigators obtain the complete body of text from the trial diary for each of their subjects and are asked to categorise "proving symptoms" in accordance to the prescribed definitions. Subsequently, a second investigator reviews coding and categorisation. In cases of contradictory categorisations, a review committee of two investigators will decide on the categorisation. At the end of this process, a list of proving symptoms for each subject will be compiled.

The categorisation of characteristic symptoms is the next step. To identify characteristic symptoms which occurred in more than one subject, an inter-subject comparison of each study arm is needed. However, investigators will still be blinded from the treatment allocation. This analysis is performed independently by two experienced investigators. The inter-coder reliability is calculated by the study statistician. The data is further structured into the following categories: localities, sensations, modalities and concomitants, times, mind and clinical findings.

Profiles of characteristic symptoms are compiled for both groups which can now be compared qualitatively.

Context analysis is the final part and will be conducted when the drug identity has been revealed at the end of the trial. The results will be related to the traditional and scientific knowledge available on the drug being investigated and discussed in the research team. The aim is to find out whether the data fits into the body of knowledge already available on the particular drug and its plausibility.

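### The context analysis judges fit to the named drug by open team discussion, with no arm masking or placebo matching stated, so it is open to confirmation bias and is not evidence of specificity

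*Protocol article*

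**What the plan says.** The Qualitative analysis section of the protocol article names three steps: coding of proving symptoms, coding of characteristic symptoms, and context analysis. The text after Figure 3 describes them.

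- **Coding of characteristic symptoms.** Two experienced investigators work independently, and the statistician calculates inter-coder reliability. On masking the text says: "However, investigators will still be blinded from the treatment allocation".
- **Profiles.** "Profiles of characteristic symptoms are compiled for both groups which can now be compared qualitatively".
- **Context analysis, timing.** "Context analysis is the final part and will be conducted when the drug identity has been revealed at the end of the trial".
- **Context analysis, reference and method.** "The results will be related to the traditional and scientific knowledge available on the drug being investigated and discussed in the research team".
- **Context analysis, purpose.** "The aim is to find out whether the data fits into the body of knowledge already available on the particular drug and its plausibility".

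Under Outcome parameters, the primary outcome is a count: "The primary outcome parameter is the number of characteristic proving symptoms per subject, derived from the qualitative data analysis". The same section adds a descriptive contrast between arms: "Qualitative differences in the profiles of characteristic proving symptoms from the homeopathic drug and the placebo will also be compared". Fit to the drug's known picture is not listed there as an outcome.

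**The concern.** Someone has to know the drug's identity in order to compare a profile with that drug's literature, so revealing it is no fault. Knowing which profile came from the drug arm is not needed for that comparison. The article names one reference drug and an open discussion. It gives no matching rule, comparator profile or mask on the arms for this step.

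The material favours chance agreement. The diaries are free text, Table 1 defines characteristic symptoms broadly, and the Discussion (Qualitative analysis) concedes that the reliability of the criteria is unclear and that results depend on the raters' experience. A team that knows both the drug and the arm can find agreement in almost any long list of symptoms.

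At stake is the secondary aim stated in the Background: a symptom profile of the drug for therapeutic use. A statement that the profile is plausible for this drug would lend it weight. That statement can be interpreted only against how well the placebo profile fits the same literature.

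**Working it through.** **1. The plan's own figures.** Sample size calculation: 30 enrolled, 20% dropout, 20 versus 15 symptoms, SD 4, two-sided 5%, 80% power.

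- 30 x (1 - 0.20) = 24 analysable.
- Standardised difference: (20 - 15)/4 = 1.25.
- The unpaired t-test (noncentral t) needs 11.09 per arm for 80% power, rounded up to 12. In total 2 x 12 = 24, and 24/0.80 = 30. The stated size reproduces. Power at 12 per arm is 83.3%.

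The article states no allocation ratio, so 12 per arm assumes 1:1. The point itself does not depend on the sample size; these figures only set the scale below.

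**2. Safeguards stated at each step.**

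| | Coding of characteristic symptoms | Context analysis |
|---|---|---|
| Masking to allocation | stated | not stated |
| Masking to drug identity | in place | lifted, as the step requires |
| Independent second rater | stated | not stated (team discussion) |
| Agreement measured | yes | not stated |
| Placebo handled the same way | profiles compiled for both groups | not stated |
| Effect on primary count | produces it | none; it comes afterwards |

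**3. Size of chance agreement.** Take no drug effect, so that both arms sit at the plan's placebo figure of about 15 symptoms per subject.

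- Symptoms per arm: 12 x 15 = 180.
- Chance that a background symptom matches the drug's literature: assumed 5-20%. The article gives no figure.
- Expected matches per arm: 0.05 x 180 = 9 to 0.20 x 180 = 36.
- Per subject: 9/12 = 0.75 to 36/12 = 3.

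Both arms give the same range, so a list of 9-36 fitting symptoms from the drug arm alone would carry no information.

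**4. Why a share and not a count.** Suppose instead that the drug arm had 20 symptoms per subject, none of them specific to the drug's literature. Symptoms: 12 x 20 = 240. Expected matches: 0.05 x 240 = 12 to 0.20 x 240 = 48. That is 240/180 = 1.33 times the placebo number, although the matching share is 5-20% in both arms. A comparison of raw match counts would repeat the difference in symptom number; the share would not.

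**The case against.** Several stronger readings are tempting, and the document does not support them.

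- **That the arms are open and the placebo profile is left out.** The article says neither. Study design treats group allocation and drug identity as two separate blinds, and only the identity is said to be revealed. The results to be discussed are not limited to the drug arm, and the sentence on profiles covers both groups. Figure 3 is not visible, and the article condenses a fuller protocol. What stands is that, as described, the step has no stated mask and no stated placebo match.
- **That the step can only favour the drug.** The stated purpose is to find out whether the data fit, so a poor fit could be reported. The risk is bias, not a fixed result.
- **That the main result is compromised.** The characteristic symptoms are coded under blinding before this step. As described, it cannot change the counts, the ANCOVA or the P-value. The article also uses drug-specific and characteristic as equivalents in its secondary aims, so its formal contrast with placebo lies in the blinded count and the comparison of profiles.
- **That a control used before was dropped without reason.** The Background reports that in recent re-proving trials "blinded homeopaths were asked to identify drug-specific symptoms in the diary of each study-subject and assign them to a list of potential homeopathic drugs". Those were well-known remedies. The same section says it is not clear that this works for new and unknown drugs, and gives that as the reason for developing the qualitative method.

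It can also be said that an interpretive discussion need not become a quantitative comparison, and that an exploratory label would prevent over-reading. The label would be a fair minimum. It would not make the fit interpretable, whereas matching both profiles would.

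**Conclusion.** The concern holds in a limited form. As described, the final qualitative step judges fit and plausibility by team discussion, with the drug known and without the safeguards stated for the coding step. That judgement is open to confirmation bias and, without the corresponding fit in placebo, is not evidence of specificity.

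In scale, 9-36 chance matches among about 180 symptoms per arm would be expected with no drug effect. This rests on 12 analysable subjects per arm (1:1 assumed), 15 symptoms per subject in both arms, and an assumed match rate of 5-20%. It shows that chance matches would be common; it does not estimate the bias.

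The consequence is confined to interpretation and to the therapeutic profile. The change is still worth making, because the better method uses data the trial already collects.

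**What to change.** Separate the two blinds at this step.

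1. Name the reference sources and the matching rule before the drug's identity is revealed, including how a subject with no characteristic symptoms is handled, since a share is then undefined.
2. Reveal the identity, but keep the arms labelled A and B.
3. Have the same team match every symptom in both profiles to those sources.
4. Lock the share of matching symptoms per subject.
5. Open the allocation and report the difference in shares between arms, labelled exploratory.

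If the full protocol already keeps the arms masked and matches both profiles, a sentence saying so would settle the point. The least that should be done otherwise is to label the context analysis exploratory and state that it does not show specificity.

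The cost is some added matching work for the placebo profile and a short delay in unblinding. No extra staff, subjects or data are needed.

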## Quantitative analysis

The main outcome will be analysed on an intention-to-treat basis by univariate analyses of covariance (ANCOVA) which includes the group (two levels), subject's expectations (ordinal with 4 levels) and the respective baseline value (linear) as covariates. From these model we will estimate the baseline adjusted treatment effect and its 95% confidence interval (CI). The reported *P*-value will be based on a two-sided t-test within this model, and a *P *< 0.05 will be considered significant. Missing values will be multiply imputed according to Rubin's suggestions [19]. In detail, 20 multiple copies of the original data set will be generated, replacing missing values by a randomly generated value according to the MCMC algorithm. Each copy will be analysed as a complete data set with the abovementioned ANCOVA model and the results will be combined appropriately. Sensitivity analyses will include some extensions of the statistical model, in this way modelling the centre as a random factor and adding the center's expectation (ordinal with 4 levels) as an additional fixed factor.

Analyses of the secondary outcome parameters will rely on the same statistical models, hereby replacing the baseline value of the main outcome parameters by the baseline value of the parameter under consideration.

All analyses will be performed using SAS/STAT^®^.

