### Randomisation and treatment allocation

Based on the "ranuni" random number generator of the SAS/STAT^® ^software, subjects will be randomly allocated to the interventions under study by block-randomisation stratified by centre (investigator). Both the centres and subjects will be coded by simple numbers unidentifiable by subjects, investigators and external persons. The random list will be sent to the Charite' central pharmacy which will prepare sealed, sequentially numbered boxes containing the study medication and send them to the centre. When a subject agrees to participate, the investigator opens the lowest numbered box and gives him/her the study medication. Each centre will keep a log file with all randomised subjects. If a subject withdraws his/her consent or discontinues to the study, he/she may not be included again. The planned flow of participants through the homeopathic drug proving trial is illustrated as flowchart in Figure 2.

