### Sample size calculation

It is planned to include 30 healthy volunteers. Assuming a drop out rate of 20%, 24 subjects will be available for analysis. In this study, an unpaired t-test with a two-sided level of 5% has a power of 80% to detect a group difference of 20 ± 4 vs 15 ± 4 (mean ± standard deviation) characteristic proving symptoms.

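### Allocation is stratified by centre but the primary ANCOVA leaves centre out; if counts correlate within centre, the test is conservative and some efficiency is given up

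*Protocol article*

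**What the plan says.** Under Randomisation and treatment allocation, the article states that "subjects will be randomly allocated to the interventions under study by block-randomisation stratified by centre (investigator"), so centre and investigator are the same unit. The Procedures section limits each investigator to three subjects. It gives that investigator the physical examination, the long homeopathic interview and the training in documentation. The investigator also telephones each subject every third day.

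Under Qualitative analysis, after the trial closes, "the investigators obtain the complete body of text from the trial diary for each of their subjects and are asked to categorise" the proving symptoms. A second investigator reviews this coding, and a committee of two settles disagreements. The characteristic symptoms, whose number is the primary outcome, are then categorised by two experienced investigators working independently.

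Under Quantitative analysis, the primary ANCOVA has three terms: group, subject's expectation (four levels) and baseline value. Centre is reserved for a secondary role: "Sensitivity analyses will include some extensions of the statistical model, in this way modelling the centre as a random factor". The sample size section uses a t-test without centre.

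**The concern.** Blocking within centre tends to put both treatments in each centre. Much of the variation between centres then cancels from the treatment comparison. A model without centre still counts that variation as residual error, so its standard error is larger than the real sampling error whenever counts are positively correlated within centre.

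The protocol gives reasons to expect some correlation. The outcome is a count of documented symptoms, and one investigator trains, interviews, calls and first codes all subjects of a centre. At stake are the width of the primary confidence interval, some power, and a foreseeable difficulty: if the two planned models fall on either side of 0.05, the one that follows the randomisation is the secondary one.

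**Working it through.** **Inputs from the article.** "It is planned to include 30 healthy volunteers"; "Assuming a drop out rate of 20%, 24 subjects will be available for analysis"; "an unpaired t-test with a two-sided level of 5% has a power of 80" per cent for a "group difference of 20 ± 4 vs 15 ± 4 (mean ± standard deviation"). At most three subjects per centre means at least 30/3 = 10 centres.

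**Assumptions, not in the article.** Allocation 1:1; blocks of 2 or 4; 10 full centres of three at entry with random dropout to 24; ICC from 0 to 0.5.

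**Step 1: the plan's own figure.** The standardised difference is (20 − 15)/4 = 1.25. With 12 per arm, SE = 4 × √(2/12) = 1.633. The noncentral t gives 83.3% power at 12 per arm and 79.6% at 11 per arm. So 24 is the smallest balanced total reaching 80%, and 24/0.8 = 30. The plan's figure reproduces, with a little power to spare.

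**Step 2: the most that omitting centre could matter.** Write the total variance as 16 and the between-centre share as the ICC. If every centre were exactly balanced, the true SE would be 1.633 × √(1 − ICC): 1.633 × √0.7 = 1.366 at ICC 0.3, and 1.633 × √0.5 = 1.155 at ICC 0.5. Centres of three or fewer cannot all be balanced, so the real reduction is smaller and has to be simulated.

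**Step 3: simulation.** 2000 runs per setting, total SD 4, difference 0 or 5, 24 analysed, blocks of 2, without baseline and expectation because the article gives no correlation for them. The random-centre model uses REML and a t reference with within-centre degrees of freedom.

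| ICC | True SE, no centre | Model SE, no centre | Type I error: no centre / random | Power: no centre / random / fixed |
|---|---|---|---|---|
| 0 | 1.63-1.64 | 1.65-1.66 | 4.6% / 5.5% | 81.9% / 80.9% / 70.1% |
| 0.1 | 1.60-1.61 | 1.64-1.65 | 4.3% / 5.2% | 83.6% / 85.0% / 76.2% |
| 0.2 | 1.56 | 1.64-1.65 | 4.0% / 5.3% | 82.0% / 84.9% / 77.1% |
| 0.3 | 1.50-1.52 | 1.64 | 3.5% / 6.3% | 85.3% / 89.1% / 82.8% |
| 0.5 | 1.40-1.41 | 1.63-1.64 | 2.4% / 5.4% | 86.3% / 96.3% / 94.6% |

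The model SE without centre is too large by 2-3% at ICC 0.1 (1.648/1.613 = 1.02; 1.640/1.599 = 1.03), 8-10% at 0.3 (1.638/1.522 = 1.08; 1.644/1.498 = 1.10) and 16-17% at 0.5 (1.633/1.409 = 1.16; 1.636/1.402 = 1.17). Monte Carlo error is about √(0.05 × 0.95/2000) = 0.5 points for type I error and √(0.85 × 0.15/2000) = 0.8 points for power.

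With blocks of 4 and 24 analysed, the results available (up to ICC 0.2) agree: 84.1% against 86.3% at ICC 0.2. A second simulation in the same layout gave losses of 3-4 points at ICC 0.3 and 4-9 points at 0.5.

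The random-centre test is itself slightly liberal at ICC 0.3 (6.3%), because its SE is about 4% too small (1.418/1.482 = 0.96). Part of its apparent gain there comes from this, and it is why the degrees-of-freedom method has to be fixed in advance.

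**Step 4: effect of the baseline covariate.** In a further simulation with the same centres, the run-in baseline was assumed to share the centre effect fully and to have a within-centre correlation of 0.5 with the outcome. At ICC 0.3, the model without centre then had type I error 5.2% and power 96.4%, against 96.5% with random centre. At ICC 0.1 both had 91.8%. When the baseline shares only part of the centre effect, part of the loss remains.

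**The case against.** The strongest reply is that no ICC is given, so no loss is established. At ICC 0-0.1 it is about one point or less. The planned ANCOVA also adjusts for baseline. Interview and training precede the run-in, so an investigator's influence on documentation may already be present in the baseline value, and Step 4 shows that full sharing removes the loss. Centre is not ignored either, since the random-centre model is prespecified. With at most three subjects per centre, the variance component is poorly estimated, and a simple primary model is a defensible choice. All of this stands and limits the size of the point. It does not remove the mismatch between how subjects are randomised and how they are primarily analysed.

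Three stronger readings should be resisted.

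- A reader might infer that omitting centre makes the primary test invalid. It does not: with positive within-centre correlation and blocking within centre, the error is on the conservative side.
- A reader might infer that the trial is underpowered as a result. The model without centre keeps 82-86% power at 24 analysed, against the 80% planned.
- A reader might infer that each investigator alone decides the primary outcome for his or her own subjects. That applies only to the first list of proving symptoms, which is reviewed. The characteristic symptoms are categorised by two independent raters, which weakens clustering through coding. The interview, training and calls still differ by centre.

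**Conclusion.** The point holds as a conditional loss of efficiency. If counts correlate within centre beyond what the baseline value explains, the primary standard error is too large and the test is conservative. The power forgone is about 0-1 point at ICC 0-0.1, 2-3 at 0.2, about 4 at 0.3 and up to about 10 at 0.5. Type I error is about 3-4% at ICC 0.3 and 2-3% at 0.5.

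The direction is secure. The size is not, because it rests on assumed ICCs, 1:1 allocation, assumed block sizes, 10 full centres at entry, and models without the planned covariates. It could be nil.

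**What to change.** Make the model with group, subject's expectation, baseline value and a random intercept for centre the primary analysis. Prespecify a small-sample degrees-of-freedom method that allows for the number of centres (Kenward-Roger is one example), and state what is done when the centre variance is estimated as zero. Keep the ANCOVA without centre as the sensitivity analysis.

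Do not use fixed centre effects. Ten centres take 9 degrees of freedom, and at 24 analysed power would be about 70% at ICC 0 and 76% at ICC 0.1.

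The change swaps the order of two analyses already planned and needs no new data or subjects. Its cost is about 1 point of power if there is no centre effect (81.9% against 80.9%).

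### The secondary-outcome sentence sends the number of serious adverse events through the symptom-count ANCOVA, which gives no test or usable interval when no event occurs

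*Protocol article*

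**What the plan says.** The Outcome parameters section of the protocol article names two secondary outcomes: the total count of proving symptoms "and the number of serious adverse events". The qualitative comparison of profiles and the inter-coder reliability follow in a separate paragraph.

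The Quantitative analysis section describes the main model as an ANCOVA "which includes the group (two levels), subject's expectations (ordinal with 4 levels) and the respective baseline value (linear) as covariates". The P-value "will be based on a two-sided t-test within this model". Missing values are imputed in 20 copies, "replacing missing values by a randomly generated value according to the MCMC algorithm". For the secondary outcomes it says: "Analyses of the secondary outcome parameters will rely on the same statistical models", with one change, "replacing the baseline value of the main outcome parameters by the baseline value of the parameter under consideration". Serious adverse events are not exempted.

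The section on classification of adverse events requires severe events to be documented separately and reported to the sponsor, the ethics committee and the authorities. It sets a reporting duty, not a different analysis.

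**The concern.** The model was written for symptom counts, for which the sample size section assumes means of 15 to 20 per subject. Serious adverse events in a small group of healthy volunteers, observed for three weeks after the first dose, are a different kind of variable. Most or all values are likely to be zero, and the run-in baseline is likely to be zero for everyone. A linear model with a t-test has little or nothing to work with there.

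This is not a detail left to an analysis plan. The article states a rule, and the rule does not suit one of the two outcomes it governs. Followed literally, it would report the one outcome that is purely about safety either as not estimable or with a P-value and interval that should not be relied on.

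**Working it through.** **Inputs from the article.** 30 volunteers planned, 24 expected for analysis after 20% drop-out (Sample size calculation). Run-in 7 days, intervention 5 days, follow-up 16 days (Procedures), so the post-dose window is 5 + 16 = 21 days. Subjects are not under treatment for any disease at inclusion (Subjects). The risk of substantial intoxication is called very low (Preclinical toxicological tests).

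**Assumptions.** The article gives no serious adverse event rate, so a range is used. It gives no allocation ratio, so 15 per arm is assumed. Each affected subject is counted as one event.

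**The plan's own figure.** The article has no figure for serious adverse events. Its sample size reproduces: with a difference of 5, SD 4 and a two-sided 5% t-test, power is 79.6% at 11 per arm and 83.3% at 12 per arm. So 24 are needed, and 24 / (1 - 0.2) = 30. This point does not touch that calculation.

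**Step 1: how likely is no event?** P(no event) = (1 - p)^30.

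| Assumed risk per subject, p | P(no event in 30) | P(at most one) |
|---|---|---|
| 0.1% | 97% | 99.96% |
| 0.5% | 86% | 99.0% |
| 1% | 74% | 96.4% |
| 2% | 55% | 87.9% |
| 5% | 21% | 55.4% |

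Up to 2%, no event at all is the most likely result.

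**Step 2: the model with no events.** Every outcome value is 0, so the estimated difference is 0, the residual variance is 0 and its standard error is 0. The t statistic is 0/0. There is no P-value, and the interval collapses to a point.

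**Step 3: the baseline term.** If nobody has a serious adverse event in the run-in, the baseline column is all zeros. With intercept, group, expectation (as one term) and baseline, the design matrix has 4 columns and rank 3. The prescribed baseline coefficient cannot be estimated. The group effect still can be, once the column is dropped.

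**Step 4: the model with a few events.** Linear model with group only, k affected of 15 in one arm and 0 of 15 in the other:

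| k versus 0 | Linear-model P | 95% CI for the difference | Fisher P |
|---|---|---|---|
| 1 | 0.326 | -0.07 to 0.20 | 1.00 |
| 2 | 0.153 | -0.05 to 0.32 | 0.483 |
| 3 | 0.072 | -0.02 to 0.42 | 0.224 |
| 4 | 0.032 | 0.02 to 0.51 | 0.100 |

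For k = 4 by hand: difference 4/15 = 0.267; residual sum of squares 4 - 16/15 = 2.933; residual variance 2.933/28 = 0.105; standard error √(0.105 × 2/15) = 0.118; t = 2.26. Fisher: 2 × C(15,4)/C(30,4) = 2 × 1365/27405 = 0.100.

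**Step 5: error rate under the null.** This used 8,000 simulated trials per rate, with group and a four-level expectation factor in the model. The test rejected in 0.0003, 0.001, 0.005 and 0.014 of trials at rates of 0.5%, 1%, 2% and 5%, against a nominal 0.05. Trials with no event count as non-rejections. Among trials with at least one event the figure at 5% is 0.0144/0.786 = 0.018.

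**Step 6: imputation, if it applies and is normal-based.** With 1 affected among 24 observed, the mean is 1/24 = 0.042 and the SD 0.204. The share of normal draws below zero is Φ(-0.042/0.204) = Φ(-0.204) = 42%.

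**Step 7: the exact alternative with no events.** The upper 95% limit is 1 - 0.025^(1/n): 21.8% for 0 of 15, and 11.6% for 0 of 30 with the arms pooled.

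**The case against.** The strongest reply is that the sentence on secondary outcomes is generic and was written with symptom counts in mind. It presupposes a run-in value, and the Abstract leaves serious adverse events out of its secondary outcomes. The Abstract also counts qualitative profile differences as secondary, and these cannot enter an ANCOVA. So the sentence cannot be meant for everything called secondary. This stands as an account of intent. It does not remove the problem, because the Outcome parameters section names only two secondary outcomes and the sentence exempts neither.

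A reader might infer that the plan will invent fractional or negative serious adverse events for drop-outs. The documents do not support that as a statement of fact. The article says only MCMC, not a normal model. The imputation text belongs to the main outcome, and it is not said to extend to this one. Severe events are documented separately, so a subject who stops the diary need not have a missing value. Step 6 is conditional.

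A reader might also infer that false safety signals will be common. Step 5 points the other way: overall the test rejects too rarely. The 4 versus 0 case is a real distortion, but it needs four affected subjects in one arm, which is unlikely at low rates.

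Finally, events reach the sponsor, the ethics committee and the authorities whatever the model does, and 0 versus 0 would be easy to read from the data. Both are true, and both limit the consequence. An upper limit of 21.8% per arm is also wide, though it states honestly what 15 subjects can show.

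**Conclusion.** The point holds as a minor, low-severity correction: the stated model is unsuited to one of the two secondary outcomes it governs.

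- **Certain from the text:** the number of serious adverse events is a secondary outcome, the ANCOVA with its own baseline is prescribed for it, and no exception is made.
- **Strictly true with no events:** no test and no usable interval. That events are rare is an assumption, plausible from the population and the short window. At 5% risk, no event has a chance of only 21%.
- **With a few events:** the model gives an answer, but its P-value and interval are unreliable. To say that it can never give a result would go too far.
- **Not established:** that imputation applies to this outcome, or that it is normal-based.

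The figures by arm rest on equal arms of 15. The primary analysis and the sample size are unaffected.

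**What to change.** In the Quantitative analysis section, restrict the sentence on secondary outcomes, and the multiple imputation, to the symptom-count outcomes. Add that serious adverse events are reported per arm as the number of events and the number and percentage of subjects affected, with exact 95% confidence intervals. The choice of safety population can be left to the analysis plan.

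The cost is one sentence. No data collection, sample size or primary analysis changes.
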